**Figure 1 F1:**
[figure not shown]
DO IT! Trial Schematic.

**Table 1 T1:** Schedule of procedures, assessments, and interventions for the DO IT! Trial (based on the SPIRIT template)

	**Study period**				
	**Pre-randomization**	**Intervention**		**Post-intervention follow-up**	**Close-out**
**TIMEPOINT**	**Year 1**	**0**	**Year 1**	**Year 1**	
	** *Sept – Nov* **		** *Sept – March* **	** *April – May* **	
	**Year 2**		**Year 2**	**Year 2**	
	** *Sept – Nov* **		** *Sept – March* **	** *April – May* **	
	**Year 3 and 4**		**Year 3 and 4**	**Year 3 and 4**	**Year 4**
	** *Sept – Nov* **		** *Sept – March* **	** *April – May* **	** *June – Aug* **
**INTERVENTIONS:**					
**‘Standard dose’ 400 IU/day**		X	X		
**‘High dose’ 2000 IU/day**		X	X		
**PROCEDURES:**					
**Informed consent**	X				
**Eligibility screen**	X				
**Randomization**		X			
**ASSESSMENTS:**					
**Baseline survey data**	X	X			
**Anthropometrics**		X			
**25-hydroxyvitamin D serum level**			X	X	
**Laboratory-confirmed URTI**			X		
**Asthma exacerbations**			X		
**Follow-up survey data**				X	
**ANALYSIS**					X

Concomitant interventions prohibited include over-the-counter multivitamins which contain vitamin D, over-the-counter vitamin D preparations and prescription vitamin D. As this is a pragmatic trial, no specific strategies are introduced to improve adherence. To monitor adherence at the end of the trial, parents are asked to return bottles and the amount of vitamin D administered is calculated based on the volume of solution remaining [94]. No specific criteria are being used for discontinuation or modification of the interventions, as the doses of vitamin D are within the safe and recommended dosages for children [70].

Block randomization occurs by study site with blocks of varying sizes to ensure that group sizes are similar at the end of each block [88]. This is particularly important in a study of vitamin D and URTI, as date of enrolment (time) may be an important covariate. Sequence generation stratified by practice site was performed centrally at the Applied Health Research Centre (AHRC) at St. Michael’s Hospital using a computer random number generator; KT (biostatistician and co-author) generated the allocation sequence. Parents, attending physicians, laboratory personnel, and study personnel conducting the outcome assessments, data analysts and investigators are blind to the group allocation. Allocation concealment is achieved by having the Pharmacy Department prepare the vitamin D preparations in sealed, serially numbered bottles identical in appearance and weight, with the drops similar in consistency and taste. Group allocation will be concealed until the final data analysis is performed.

### Outcomes and measures

The *primary outcome* is the number of laboratory-confirmed viral URTIs per child over the winter months. Because of the wide variety of respiratory viruses and URTI illness presentations, signs and symptoms of viral URTI are non-specific and may not be reliably measured by parental report [95,96]. Therefore, in addition to parents of enrolled children completing a symptom checklist with each URTI (see Additional file 3: Symptom Checklist), parents are asked to obtain a nasal swab from their child. Nasal swabs done by parents have been shown to be as effective in detecting respiratory viruses as those obtained by health professionals but less invasive and better tolerated [97]. Parents are instructed to place the swab in provided viral transport media and refrigerate until couriered to the study laboratory (Mount Sinai Services) within 24 hours [44,98]. Respiratory viruses are identified using reverse transcriptase polymerase chain reaction (RT-PCR) technology. RT-PCR is performed on each sample which has a sensitivity of 95% and specificity of 100% for the identification of respiratory RNA viruses, which is more sensitive than viral culture and comparable to immunofluorescence [99]. Samples are tested for 18 common respiratory viruses including influenza A and B, adenoviruses, respiratory syncytial virus (RSV), picornaviruses (enteroviruses and rhinoviruses), coronovirus, metapneumovirus and parainfluenza virus using the ID-Tag™ RVP assay using the Luminex xMAP™ system (Cat# R019A0105, TM Bioscience Corp., Toronto, ON) [100]. This is the same assay and machine that is routinely used in the Ontario public health laboratories.

*Secondary outcomes* include parent reported URTI, specific viral agents that cause URTI (influenza, adenovirus and RSV), asthma exacerbations among children with asthma, physician-diagnosed otitis media and pneumonia, emergency department visits and hospitalizations, collected by monthly telephone call and confirmed by review of the child’s clinic medical record. Follow-up 25-hydroxyvitamin D serum level is measured to determine the vitamin D dose vs. serum response relationship. Finally, change in 25-hydroxyvitamin D serum level from baseline is determined to document that an improvement in health outcomes is mediated through an increase in 25-hydroxyvitamin D serum level.

Parent reported URTI symptoms are defined as two or more of fever (>38°C), cough, runny nose, sore throat, headache, vomiting, feels unwell, muscle aches, ear ache or infection, poor appetite, not sleeping well, cranky/fussy, low energy or crying more than usual from a validated parent completed symptom checklist (CARIFS) collected with the viral sample. CARIFS has been developed, validated and extensively used by our team and others [101,102]. A new URTI cannot commence until ≥ 3 symptom free days since the end of a previous URTI [44].

Asthma is defined as parental report of asthma plus confirmation from the child’s medical record of 2 or more episodes of wheeze requiring the prescription of inhaled asthma controlling medications [103]. An asthma exacerbation is defined as a wheezing episode in children with asthma as obtained from parent completed symptom checklist based on the International Study of Asthma and Allergies in Childhood (ISAAC) [103].

Blood is drawn by trained pediatric phlebotomists from the antecubital vein for determination of 25-hydroxyvitamin D serum levels. Specimens are sent to the Clinical Biochemistry Laboratory at the Mount Sinai Hospital with the study requisition, where they are processed according to standard procedures. Total 25-hydroxyvitamin D is measured from serum samples using a competitive two-step chemiluminescence assay which has been validated for measurement of 25-hydroxyvitamin D in children older than 1 year of age [104]. The specific instrument that is used to analyze all samples is a Diasorin LIAISON® 25-hydroxyvitamin D TOTAL [105]. This technique and instrument have been chosen to be consistent with national vitamin D surveys from both Canada and the United states [19,27]. Extensive testing and validation of this machine has been performed and has demonstrated an intraassay imprecision of 7.2% at a concentration of 213 nmol/L and an interassay imprecision of 4.9% at 32 nmol/L, 8.9% at 77 nmol/L and 17.4% at 213 nmol/L, values which are well within acceptable limits for biochemical measurements. During this study, the instrument is monitored using the UK DEQUAS external quality assessment scheme which is an internationally recognized vitamin D quality assessment protocol [106].

### Recruitment and retention

Since June 2008, over 4500 children age 1–5 years have been recruited through *TARGet Kids!* practices with collection of questionnaires (demographics, lifestyle factors) and anthropometric measures (height, weight and waist circumference). Since December 2008 venous blood samples have been collected from over 2500 children [107]. *TARGet Kids!* is now operating out of seven sites with over 100 children per month being recruited with phlebotomy. Therefore, recruitment of 750 children in September through November over 4 consecutive seasons for this study is feasible.

We expect that there will be a different spectrum of infections as respiratory virus incidence, distribution and severity tend to vary from year to year.

Strategies to achieve adequate recruitment include approaching eligible subjects during a well-child visit. Lists of children scheduled for a well-child visit are reviewed in advance. An information package is mailed to each family 2 to 4 weeks prior to the visit inviting them to participate. This allows parents time for consideration in advance and reduce coercion to participate. Parents are approached in person by the research assistant while registering for the clinic visit. At the initial visit, baseline survey data, anthropometric measures, and baseline vitamin D serum level are collected.

Strategies for retention include a monthly telephone call to encourage collection of nasal swabs and completion of symptom checklists. Every reasonable attempt is made to locate patients at follow-up. Topical anesthetic cream (EMLA or Ametop) is offered to minimize discomfort from venipuncture. Blood is drawn in the primary care physician’s office negating the need to attend a separate laboratory visit. Parents who have moved out of district are offered to visit The Hospital for Sick Children for repeat laboratory testing. Should these efforts fail to obtain a blood sample, a home visit for phlebotomy is offered. This is expected to occur in less than 10% of subjects.

### Follow-up data collection and data management

Parents of participating children receive a monthly telephone call by a research assistant reminding them to administer the vitamin D supplement daily and record the number of asthma exacerbations, emergency department visits, hospitalizations and missed work days. Parents are also be reminded to collect nasal swabs and complete symptom checklists. In addition, parents are asked to return to their child’s physician’s office in April or May to capture peak respiratory virus season. At the follow-up visit, blood is drawn for 25-hydroxyvitamin D level and a follow-up data collection form completed. The following potential co-interventions are also measured: influenza vaccination, dietary vitamin D intake using a 3 day dietary recall [86], over-the-counter vitamin and mineral supplementation (i.e., calcium containing multivitamins), herbal remedies (i.e., echinacea) and hours per week in daycare (see Additional file 4: Follow-up Data Collection Form). This methodology has been used successfully by our group and others [44,45,98].

To ensure high quality data collection, research assistants are trained in the accurate completion of questionnaires, anthropometric measurement and are registered pediatric phlebotomists as per standard *TARGet Kids!* operating protocol. Weight is measured using a precision digital scale (±0.025% SECA, Hamburg Germany), standing height is measured using a stadiometer (SECA, Hamburg Germany), and skin pigmentation is measured using a narrow-band reflectometer (Dermaspectrometer, Cortex Technology) [108-111]. Questionnaires and URTI symptom checklists have been pilot tested to ensure understandability and reduce incomplete responses [101]. Collected data is electronically entered on a daily basis by research assistants at each site into the study’s central database via a secure web-based data portal.

The Applied Health Research Centre (AHRC) of the Keenan Research Centre, Li Ka Shing Knowledge Institute of St. Michael’s Hospital houses this central database and is the data management centre for this study (under the direction of MM, co-author). AHRC employs state-of-the art web-based data management software: Medidata RAVE™ (5.6.3) by Medidata Solutions Inc. RAVE™ uses secure encrypted web-based data capture technology and is the data repository for data collected during this study. RAVE™ is an industry-leading electronic data capture and clinical data management system, with user configurable workflows, sophisticated case report form (CRF) design, complex edit checking, and customized security parameters. RAVE™ allows our research assistants to enter data remotely in real time to the central database from any of the practice sites. RAVE™ has extensive built in reporting capabilities, and data can be exported to standard formats for data analysis (e.g., SAS). Laboratory tests are directly uploaded to RAVE™ through a secure web portal. These features enable *TARGet Kids!* to be highly efficient and are vital to the success of this study.

### Sample size

The sample size was based on asymptotic methods for a likelihood ratio test assuming a Poisson distributed outcome and was confirmed by simulation studies. All sample size and power calculations assume a 5% Type I error probability (two-sided). If we assume an average of one URTI per month during a minimum of 4 winter months [42,44-49] among children receiving the standard dose of vitamin D, we would therefore expect an average of four URTI per child over the winter. A sample size of 300 per group would give 90% power to detect a reduction in the average number of URTI per winter of one URTI. We believe that, even one fewer URTI over the winter would be a clinically important outcome, especially to families with young children. Although the study is not powered to detect reductions of specific kinds of infections, a conservative estimate is that at least 25% of children will have one of RSV, adenovirus or influenza which collectively result in the greatest burden of illness in this population [44,50], this sample size gives 80% power to detect a 50% absolute reduction in this composite outcome. Preliminary *TARGet Kids!* data suggests an 80% retention rate [107,112]; therefore, to accommodate a 20% loss to follow-up, 375 children will be recruited to each group (750 total).

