### Viral upper respiratory tract infection

Viral upper respiratory tract infections (URTI) are the most common infectious disease in North America [42]. URTI is the most common reason for emergency department visits and unscheduled outpatient visits in Canada comprising 10% of emergency department visits for children under 10 years of age [2,43]. Preschoolers have the highest incidence of URTI of any age group, occurring 1–2 times per month per child during the winter and higher among children who attend daycare [42,44-49]. Influenza, RSV and adenovirus, which collectively comprise 25% of respiratory infections in children, are the most common viruses that lead to febrile illness, acute otitis media, outpatient visits and hospitalization [44,50]. Roughly 50% of preschoolers with URTI are brought to medical attention resulting in an additional outpatient physician visit every 2 to 3 months during the winter with 1% requiring hospitalization [44,51]. Several groups have estimated the direct and indirect costs of URTI in preschoolers to be between $261 and $276 per URTI with influenza being the most costly virus, contributing $809 per URTI [45,51]. The collective cost of URTI in children under 5 years of age has been estimated to be $1.8 billion annually in the US [52]. Evidence supporting a causal connection between low vitamin D serum levels and URTI comes from multiple sources.

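### The sample-size paragraph gives its rate and target for URTI without saying laboratory-confirmed, and its 90% power at 300 per group does not follow from 4 versus 3

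*Protocol article*

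**What the plan says.** The Sample size section rests on "asymptotic methods for a likelihood ratio test assuming a Poisson distributed outcome and was confirmed by simulation studies", with a two-sided 5% type I error. Its rate for the standard-dose group is introduced by "If we assume an average of one URTI per month during a minimum of 4 winter months", and it continues that "we would therefore expect an average of four URTI per child over the winter". The effect sought is "a reduction in the average number of URTI per winter of one URTI". On these inputs it states 90% power with 300 children per group, and recruits 375 per group to allow for 20% loss to follow-up.

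The rate carries the same reference numbers as the Background section on viral URTI, which describes URTI in preschoolers as "occurring 1–2 times per month per child during the winter", and higher in daycare.

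Outcomes and measures defines the primary outcome as the "number of laboratory-confirmed viral URTIs per child over the winter months". An event counts only if a parent takes a swab, it is refrigerated and couriered, and RT-PCR is positive. The reason given is that "signs and symptoms of viral URTI are non-specific and may not be reliably measured by parental report". Parent-reported URTI is listed separately, as a secondary outcome. The Statistical analysis section applies the Poisson model to laboratory-confirmed URTI and mentions a negative-binomial model if there is overdispersion.

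**The concern.** The planning mean and the target are stated for URTI in general terms, while the endpoint that they are meant to support is narrower. Some symptomatic episodes will not be swabbed; the monthly calls to encourage swabbing show that this is foreseen. Some swabs will be negative, and the assay's stated sensitivity is 95%. The only allowance in the paragraph is for loss to follow-up. A reader therefore cannot tell what confirmed count per child the trial was planned on, nor what one fewer means for that count. One fewer is a 25% reduction from a mean of 4, 50% from 2, and 100% from 1. The economic analysis also works per laboratory-confirmed URTI avoided, so the confirmed rate matters there as well.

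The stated power is the natural place to look for the confirmed rate that was intended. It does not help, because it does not follow from the inputs given.

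**Working it through.** **Inputs from the Sample size section:** m0 = 4, m1 = 3 (rate ratio 0.75), two-sided 5%, 90% power, 300 per group, 20% loss. **Not in the document:** the expected confirmed mean and any dispersion. These are assumed below and shown as a range.

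**Step 1: reproduce the stated figure.** For two Poisson means on the log scale,

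n per group = (1.960 + 1.282)² × (1/m0 + 1/m1) / (ln(m1/m0))²

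= 10.507 × (1/4 + 1/3) / 0.2877² = 10.507 × 0.5833 / 0.0828 ≈ 74.1, rounded up to 75.

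The likelihood-ratio, rate-difference and square-root versions each give 74. A simulation of the likelihood ratio test (20,000 runs) gave 90.3% power at 74 per group and 100% at 300. So 300 per group is not what 4 versus 3 requires. At 300 the power for 4 versus 3 exceeds 99.99%, and 90% power is reached for a reduction of about 0.51 from 4. The step to 375 is correct: 300 / 0.80 = 375.

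**Step 2: what 300 per group does fit.** Let φ be the ratio of variance to mean. With m1 = 0.75 m0,

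power = Φ( 0.2877 / √[φ(1/m0 + 1/m1)/300] − 1.960 ) = Φ( 3.262 × √(m0/φ) − 1.960 ).

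Power depends only on m0/φ, and 90% needs m0/φ ≈ (3.242/3.262)² ≈ 0.99. Two readings meet this:

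- means of about 1 versus 0.75 with φ = 1 (n = 293 to 297 by the different formulas; power 90.4% at 300);
- means of 4 versus 3 with φ ≈ 4.05 (a negative-binomial dispersion of about 0.89).

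The document states neither.

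**Step 3: power at 300 per group for a rate ratio of 0.75.** The confirmed means and φ are assumptions.

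| Confirmed mean, standard dose | Power, φ = 1 | Power, φ = 2 | One fewer as a relative reduction |
|---|---|---|---|
| 4 | >99.9% | 99.6% | 25% |
| 2 | 99.6% | 90% | 50% |
| 1 | 90% | 64% | 100% |
| 0.8 | 83% | 54% | not possible |

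Example: mean 2, φ = 2 gives 3.262 × √1 − 1.960 = 1.302, so 90%. Mean 1, φ = 2 gives 3.262 × √0.5 − 1.960 = 0.347, so 64%.

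**Step 4: could the low-end rate already allow for incomplete capture?** The Background gives 1–2 per month, and the Intervention section gives 4–8 months of supplementation with viruses circulating November through April. Four months at 2 per month is 8 episodes, so a confirmed mean of 4 would need 4/8 = 50% capture. Six months at 1–2 per month is 6–12 episodes, so it would need 4/6 = 67% down to 4/12 = 33%. At 1 per month over four months it would need 100%. The document does not say which applies.

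**The case against.** The strongest reply is that the rate may already be suitable for the primary endpoint. The cited sources cannot be read here, and at least one of them is also cited for the swab handling procedure, so some may have counted virologically confirmed infections. Four is also a floor: the bottom of the monthly range over the minimum number of months. Step 4 shows that a confirmed mean of 4 is then compatible with capture well below 100%. This stands. A reader might infer that the plan assumes every URTI is swabbed and positive, or that the true confirmed mean must be four times the capture share. The document supports neither, and 90% power at 300 would itself be an odd result of full capture at 4 versus 3.

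A second reply is that the full protocol, which is not shown, may hold the missing rate or dispersion, since the article says that simulation confirmed the size. That is possible. It does not repair the paragraph, which gives inputs and a result that do not agree.

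A third reply is that one fewer URTI is a planning target and not a success criterion. The trial is a superiority comparison by Poisson regression, so nothing in the plan judges it against that difference. This also stands, and it limits the harm.

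**Conclusion.** The concern holds as a defect in what the sample-size paragraph states. Its rate and target are not tied to laboratory-confirmed URTI, no expected confirmed rate is given, and 90% power at 300 per group does not follow from 4 versus 3 under the stated Poisson test, which needs about a quarter of that number.

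A reader might go further and conclude that the trial is underpowered, or that it is aimed at an effect it could not show. The document does not support that. With Poisson counts, 300 per group keeps 90% power for a 25% reduction down to a confirmed mean of about 1. With variance twice the mean, it keeps 90% down to a mean of about 2. Power falls clearly below 90% only if the confirmed mean is below about 1, or if low capture and overdispersion occur together, as in the 64% at a mean of 1 with φ = 2. The document gives neither the confirmed mean nor the dispersion, so these figures are conditional.

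**What to change.** Restate the sample-size paragraph for the primary endpoint:

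- Give the expected number of confirmed URTI per child in the standard-dose group, as reported rate × share swabbed × share PCR-positive, with the source of each term. If the cited rate is already a confirmed rate, say so.
- State the dispersion assumed.
- Express the target as a rate ratio, for example 0.75, so that it keeps its meaning whatever the capture.
- Replace the single 90% with power at 300 per group over a range of confirmed means and dispersions, as in the table above.
- Check the assumed mean against the pooled first-winter confirmed rate, blinded to allocation. Under a rate ratio of 0.75 with equal groups, the pooled mean is 0.875 times the standard-dose mean; a standard-dose mean of 2 would show as 1.75.

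The cost is a rewritten paragraph, a small table and one blinded tabulation. Endpoint, analysis and enrolment stay as they are. The stated power may look less favourable in some cells of the table.

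### The stated 90% power at 300 per group does not follow from the stated assumptions: Poisson means of 4 versus 3 give over 99.9% power, and 90% needs about 74 per group

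*Protocol article*

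**What the plan says.** The Sample size section of the protocol article gives the following planning basis.

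- **Model and test:** asymptotic likelihood ratio methods, "assuming a Poisson distributed outcome and was confirmed by simulation studies".
- **Type I error:** 5%, two-sided.
- **Control mean:** "If we assume an average of one URTI per month during a minimum of 4 winter months", from which "we would therefore expect an average of four URTI per child over the winter".
- **Effect and power:** "300 per group would give 90% power to detect a reduction in the average number of URTI per winter of one URTI".
- **Loss to follow-up:** 20%, which takes 300 to 375 per group and 750 in total.

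The section states no overdispersion, clustering allowance or other inflation. The Statistical analysis section mentions overdispersion only as a reason to consider a negative binomial model at the analysis stage.

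**The concern.** A Poisson model has no free variance parameter. Once the two means, the significance level and the group size are given, the power is determined. The section prints all of these beside the result, and the two disagree by a factor of about four in sample size.

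The sentence carries the whole justification for the number of children in the primary analysis and defines the effect the trial is said to detect. As written, three trials are possible: one with far more power than claimed, one planned on a much lower event count than four, or one planned with a large unstated overdispersion. They differ in what a null result would mean. A reader who takes the text at face value would set such a result against a one-URTI effect, although under the stated model the trial could detect about half of that.

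**Working it through.** **Inputs** (all from the Sample size section): control mean a = 4; intervention mean b = 4 − 1 = 3; Poisson, so variance equals mean; two-sided α = 0.05; n = 300 evaluable per group. The planned loss confirms that 300 is the number after dropout: 300 / 0.8 = 375.

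**Step 1. Try to reproduce 90% with the named test.** The noncentrality of the Poisson likelihood ratio test (1 df) is n × 2[a ln(a/m) + b ln(b/m)], with m = (a + b)/2 = 3.5.

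- Per child: 2[4 ln(4/3.5) + 3 ln(3/3.5)] = 2[0.5341 − 0.4625] = 0.1433.
- At n = 300: 300 × 0.14335 = 43.0.
- Power: 0.999998. The Wald test on the rate difference agrees to five decimals. A simulation of 200,000 trials gives 1.000.

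The stated 90% does not reproduce.

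**Step 2. Sample size for 90% power.** (1.960 + 1.2816)² = 10.507.

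| Method | Formula | n per group |
|---|---|---|
| Likelihood ratio | 10.507 / 0.14335 | 73.3 |
| Rate difference | 10.507 × (4 + 3) / 1² | 73.6 |
| Log rate ratio | 10.507 × (1/4 + 1/3) / ln(0.75)² | 74.1 |
| Square root | 10.507 / [2(√4 − √3)²] | 73.2 |

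All give about 74 per group, and simulated power at 74 is 90.3%. With 20% loss: 74 / 0.8 = 92.5, so 93 per group.

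**Step 3. What 300 per group detects with 90% power at a control mean of 4.** Solving 10.507 / {2[4 ln(4/m) + b ln(b/m)]} = 300, with m = (4 + b)/2, gives b ≈ 3.49. That is a reduction of about 0.51 URTI, or 0.51 / 4 ≈ 13%.

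**Step 4. Other readings of the text.**

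| Reading | Power at 300 per group |
|---|---|
| Longer follow-up, 6 vs 5 | 99.9% |
| Longer follow-up, 8 vs 7 | 99.4% |
| 4 vs 3, but 240 per group | 99.995% |
| 4 vs 3, variance 2 × mean | 99.6% |
| 4 vs 3, variance 3 × mean | 96.6% |
| 4 vs 3, variance 4 × mean | about 90.5% |
| 4 vs 3.5, Poisson | 88.6% |
| 1 vs 0.75, Poisson | 90.6% |

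Three departures from the text come close to 90%:

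- **Variance about four times the mean.** The exact ratio is 300 / 74.1 ≈ 4.05 on the log scale and 300 / 73.6 ≈ 4.08 on the difference scale. This contradicts the Poisson assumption.
- **A reduction of half an URTI rather than one.**
- **A mean of 1 versus 0.75 per child**, which needs 293 to 296 per group. This is what results if the monthly rate is used without multiplying by four months of exposure. It would explain the factor of four, but it is an inference; the article does not show how the figure was obtained.

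**The case against.** The strongest reply accepts the arithmetic and disputes its importance. The error is conservative: on the printed inputs the trial has more power than claimed for the effect called clinically important. Nothing in enrolment or analysis changes, and the planned number still gives about 90% power for one URTI if the variance is four times the mean. Since the Statistical analysis section foresees possible overdispersion, a margin is not unreasonable. A null result would in any case be read mainly from the rate ratio and its confidence interval. Follow-up is also given as a minimum of four months, so exposure has a floor rather than a fixed value.

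Much of this is fair. The trial is not harmed in conduct, a margin for overdispersion may be sensible, and the origin of the figure cannot be settled from the article. None of it makes the 90% correct. The Sample size section claims no margin; it names a Poisson outcome and says simulation confirmed the result, yet simulating the printed inputs gives essentially 100%. Longer follow-up leaves power above 99%.

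One warning about the remedy does stand. Printing 90% power for half an URTI would be true under pure Poisson variation alone. With variance two or three times the mean, the reduction detectable from 4 rises to about 0.71 or 0.86.

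**Conclusion.** The concern holds. For a Poisson outcome with means of 4 and 3, two-sided 5% and 300 evaluable children per group, power is 99.9998%, not 90%. The number needed for 90% is about 74 per group (93 with 20% loss), roughly a quarter of the number stated. The effect detectable with 90% power at 300 per group is about 0.51 URTI per winter, half of the one stated.

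These results rest only on inputs printed in the Sample size section, and four formulas and a simulation agree. The dropout step is correct. The misstatement overstates the required sample size rather than understating it, so the trial is not short of power for one URTI under its own assumptions. It should still be corrected, because it is the primary power statement and does not follow from its own terms.

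**What to change.** Keep 750 children and rewrite the power paragraph in one of two ways.

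1. **Preferred:** state the mean count per child and the dispersion actually used in the calculation and simulations, with the effect that matches. Examples are a mean of 1 versus 0.75 per child, or 4 versus 3 with variance about four times the mean. If overdispersion was assumed, the paragraph should no longer describe the basis as Poisson.
2. **If the basis really was Poisson with a mean of 4:** state that 300 per group gives over 99.9% power for a reduction of one URTI and 90% for about 0.5. Add the detectable reduction under overdispersion, for example about 0.71 and 0.86 URTI at variance two and three times the mean, so that the Poisson figure is not read as a guarantee.

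The cost is one paragraph. It requires no more children, no new procedures and no change to the analysis.
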